#### **2.4.3 Study design**

A cluster-randomized controlled trial will be used in this study with teams as units of randomization.

#### **2.4.4 Participants**

Coaches and assistant coaches of the teams in the second division teams will participate in this study. The coaches have been the center of focus in recent years as the main actors in the development of soccer in Rwanda. Much training has been organized by FIFA and CAF to enhance the knowledge and practice of the coaches. Trainings pertaining to technical, tactical and physical performance of the players were provided. At the end of the training, coaches are provided certificates. Not all coaches in Rwanda are citizens and not all of them had the same training. There are therefore some differences that may arise from their coaching training, background and experience.

The coaches are required to plan and supervise training sessions to develop the fitness and the skills of the payers. Coaches are responsible for the development of the training sessions according to the demands of the competition and the period of the season. The involvement of the coach in the first division teams concerning injuries in Rwanda is relatively less compared to the coaches in the second division because the teams have medical personnel who provide assistance. They also have assistant coaches, sometimes goalkeeper coaches, and kit managers. Coaches in the second division do not have all the support needed for their work. Working with

young players, they are required to act as organizers, parents, teachers, counselors, discipliners, for them to achieve results. In the case of injuries, coaches are looked at as mature and responsible people to provide first aid, preliminary management and advice for treatment. Coaches are further responsible to allow the players to return to play after injuries.

There are 19 teams in the second division and each team has at least one head coach. The minimum number of coaches of the teams who will receive the training is 19. The assistant coaches and goalkeeper coaches of the teams in the intervention study will also participate in the study even though not all the teams have them. The total number of players participating in the in the second division league is 570.

#### **2.4.4.1 Inclusion criteria**

Head coaches and their assistants as well as goalkeeper coaches of the teams participating in the second division league will be included in this study. Players who have contracts and licenses of teams enrolled to play in the second division will be included in the study. Players presenting injury at the beginning of the study will be included when cleared to join teams' training and matches. Players with injuries at the start of the study will be included, but the pre-existing injuries will not be included in data analysis. Players or teams that will leave or join the league before the end of the study will be included in the analysis for their time of participation.

#### **2.4.4.2 Exclusion criteria**

Players and coaches who will not agree to participate in the study will be excluded from the study.

#### **2.4.4.3 Sample size / power analysis**

Based on the study conducted by Twizere (2004), about 70% of soccer players in Rwanda sustained injuries. To obtain a 20% reduction of injuries with the implementation of the 11+ programme with the power of 90% and alpha of 5%, a sample size of 125 in each group (intervention and control) will be required. Taking into consideration the design effect of 2 for cluster randomization, the minimum number of players that should participate in this study is 217.

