### **2.3.9 Statistical analysis**

All data will be analyzed statistically using STATISTICA version 12. Standard descriptive statistics will be used for numerical variables as means, standard deviations (SD) or 95% confidence intervals (CI).

In this study incidence for all injuries will be expressed as injuries per 1000 soccer playing hours for the purpose of the comparison with previous epidemiological studies. Risk per 1000 hours of exposure either per match, training or both will be equal to number of injuries multiplied by 1000 per total exposure time. The variations of injuries during match, training or both for the two seasons will be analyzed using Analysis of Variance (ANOVA). ANOVA will also be used to analyze the occurrence of injuries according to the position in the team and division of play. The categorical variables such as the frequency, type, location, severity as well as the mechanism of injuries will be analyzed using a Chi-square test or Fisher's exact test for small numbers. Between groups incidence of injuries will be compared using z-statistics and rate ratios (RR) with a 95% CI will used to present data. The level of significance for all the tests is set to 0.05. Univariate and multivariate regression analyses will be used to calculate odds ratios (ORs) and 95% confidence intervals (CIs) for  $\pm 1$  standard deviation of change. The details of all the statistical analysis that will be performed are provided in the appendix J.

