#### **2.4.2.1 Objectives**

- a. To assess if there is any difference in the occurrence of injuries before and after the introduction of the injury prevention warm up programme
- b. To assess if the compliance of the injury prevention warm up programme will be associated with the reduction injuries.
- c. To determine if there are any differences in injury incidence and exposure time between groups or over time

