#### **2.4.8 Statistical analysis**

Analysis of the incidence of injuries comparing the two study groups and the two divisions will be done as explained in the study one. Demographic characteristics of the coaches and responses on the knowledge, perception, readiness and decision making assessment will be analysed using descriptive statistics (range, mean, standard deviation). Categorical data like the coaches’ level of education, highest level of coaching license, availability of the medical personnel into the team will be presented as frequency and percentages. The five injury prevention readiness to practice questions will be coded from zero to five. The minimum score will be zero and the maximum score will be 25. The responses from the perception questions that are on a 5-point Likert scale will be recorded on a range from 1=“very unlikely” to 5=“very likely”. Therefore the results will be analysed using the descriptive statistics with means and standard deviation. Pearson correlation will be used to assess the relationship between perception variable and coaches’ readiness of sports injury prevention. The same test will be used to assess the association between readiness, perception, and first aid knowledge and compliance with the injury prevention programme. Analysis of variance test (ANOVA) will be used to analyse the difference between the coaches’ perceptions, knowledge, and readiness regarding injury prevention in the first division and the second division. The level of significance for all the tests

is set to 0.05. The details of all the statistical analysis that will be performed are provided in the appendix J.

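### The stated 90% power is for a 20-point drop in the share of players injured (about a 42% lower rate), not for a 20% relative reduction or for the planned rate-ratio test

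*Combined protocol and SAP*

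**What the plan says.** Section 2.4.4.3 starts from a proportion, "about 70% of soccer players in Rwanda sustained injuries", taken from an earlier Rwandan study. It gives no observation period, exposure time or number of injuries per player. It continues "To obtain a 20% reduction of injuries with the implementation of the 11+ programme with the power of 90% and alpha of 5"%, and concludes that "a sample size of 125 in each group (intervention and control) will be required". It does not say whether the 20% is absolute or relative. It then names a design effect of 2 and a minimum of 217 players.

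The outcome to be compared is on another scale. Objective (c) in 2.4.2.1 is "To determine if there are any differences in injury incidence and exposure time between groups or over time". Section 2.4.8 says "Analysis of the incidence of injuries comparing the two study groups and the two divisions will be done as explained in the study one". Section 2.3.9, to which this points, expresses incidence as injuries per 1000 playing hours and says "Between groups incidence of injuries will be compared using z-statistics and rate ratios". No primary outcome is named. Section 2.4.4 puts the second division at 19 teams and 570 players.

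**The concern.** The sample size rests on whether a player is injured at all. The between-arm comparison of incidence counts every injury against hours of exposure. Power for one does not carry over to the other without a mean number of injuries per player, which the supplied text does not give.

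The unlabelled 20% makes this worse. Next to an analysis of rates, a 20% reduction of injuries reads most naturally as a rate ratio of 0.80. If 125 per group was computed for a much larger effect, a null result would be reported as coming from a trial with 90% power to find a 20% reduction, when its power for that effect could be far lower.

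**Working it through.** **Inputs from the documents:** 70% injured, a 20% reduction, power 90%, alpha 5%, 125 per group, design effect (DE) 2 (all 2.4.4.3); 570 players (2.4.4), so 285 per arm if the arms are equal.

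**Assumptions:** two-sided test, equal exposure per player, and a mean number of injuries per control player, m, which is varied below.

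**1. The plan's own figure.** With p̄ the mean of the two proportions, n per group = [1.960√(2p̄(1−p̄)) + 1.282√(p₁(1−p₁) + p₂(1−p₂))]² / (p₁−p₂)².

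- 70% vs 50%: (1.358 + 0.869)² / 0.04 = 124. This matches 125, and 125 per group gives 90.2% power.
- 70% vs 56% (20% relative): (1.338 + 0.866)² / 0.0196 = 248. Here 125 per group gives 63% power before any clustering.

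So 125 means a drop of 20 percentage points.

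**2. Relative 20% on the proportion scale, whole league.** With DE 2 the effective size is 285/2 = 142.5 per arm. Power = Φ[(0.14√142.5 − 1.338)/0.676] = Φ(0.49) = 69%. For 70% vs 50% the same size gives 94%.

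**3. Moving to rates.** If counts are Poisson and 30% of players are uninjured, m = −ln 0.30 = 1.204. Then 50% injured corresponds to a rate ratio (RR) of ln 0.50 / ln 0.30 = 0.576, a 42% lower rate. A 20% lower rate moves the proportion injured only from 70% to 1 − 0.30^0.8 = 62%.

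**4. Power of the rate comparison, 285 per arm, DE 2.** Variance of ln RR: v = 2 × [1/(285m) + 1/(285m·RR)]. Power = Φ(|ln RR|/√v − 1.960).

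- RR 0.80, m = 1.204: 343 and 275 injuries expected, v = 0.0131, √v = 0.1145. Power = Φ(0.2231/0.1145 − 1.960) = 49.5%. A t reference on 17 df (19 teams) gives 45%.
- RR 0.576, m = 1.204: √v = 0.1263. Power = Φ(0.552/0.1263 − 1.960) = 99%.

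**5. Sensitivity.** The last column solves the step 4 formula for the RR that has 90% power. For overdispersion between players with parameter k (negative binomial, 70% injured kept), 1/m becomes 1/m + k in each arm, and likewise for 1/(m·RR).

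| Assumption (570 players, DE 2) | Power for RR 0.80 | RR detectable at 90% |
|---|---|---|
| m = 0.7, Poisson | 32% | 0.59 |
| m = 1.2, Poisson (70% injured) | 50% | 0.68 |
| m = 2, Poisson | 71% | 0.75 |
| m = 3, Poisson | 87% | 0.79 |
| k = 0.5, m = 1.65 (70% injured) | 41% | 0.65 |
| k = 1, m = 2.33 (70% injured) | 34% | 0.62 |

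At DE 2 and Poisson counts, 90% power for RR 0.80 needs about 3.3 injuries per control player.

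**The case against.** The strongest reply is that the plan powered 70% against 50%, and that carrying this effect to the rate scale costs nothing: the whole league then has about 99% power. This stands. The shortfall comes from the size of the effect, not from the change of scale alone. A reader might infer that the trial is underpowered as a whole. The documents do not support that for the effect behind 125 per group.

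A reader might also take about 50% as the most power the league can offer for a 20% lower rate. That is not a bound either. The 70% has no stated period, and section 2.3.5.4 counts any physical complaint whether or not it needs medical attention, so injuries per player could exceed 1.2. Poisson means of 2 and 3 do imply 86% and 95% of players injured (1 − e⁻² and 1 − e⁻³), which departs from the plan's 70%, and keeping 70% with overdispersion lowers power. Without a period for the 70%, though, the higher means cannot be excluded.

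The rate ratio is not the only planned test. Section 2.3.9 also lists chi-square tests on frequencies and regressions giving odds ratios, and full details are left to Appendix J, which is not in the supplied text. A comparison of players injured may be planned there. The main text would still attach 90% to a reduction it does not define, and would give no power for the incidence comparison it does describe.

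Finally, 125 is not miscalculated. The 217 is a separate problem: 125 × 2 groups × 2 = 500. It should be reconciled on its own account.

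**Conclusion.** Wrong as written. The 90% holds, before clustering, for a 20-point drop in the proportion injured. It is not shown for the rate ratio, and it is not reached for a 20% relative reduction on either scale: about 69% for 70% vs 56% injured, and about 50% for a rate ratio of 0.80.

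Both figures assume all 570 players, equal arms and a design effect of 2. The second also assumes equal exposure and 1.2 injuries per player. It falls to between 41% and 34% with overdispersion of k = 0.5 to 1 at 70% injured, and runs from 32% to 87% over an assumed 0.7 to 3 injuries per player. Every case in that range is below 90%.

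**What to change.** Rewrite the power paragraph in 2.4.4.3 to do four things:

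- Say that the 20% is an absolute drop in the proportion of players injured, 70% to 50%.
- Name the between-arm injury rate ratio as the outcome to which power refers.
- Replace the 90% claim with the detectable effect and its assumptions. For example: with 19 teams, at most 570 players and a design effect of 2, the trial has 90% power for a rate ratio of about 0.68 if control players average 1.2 injuries (Poisson), 0.62 with overdispersion k = 1 and 70% injured, and 0.59 to 0.79 for averages of 0.7 to 3.
- Commit to recalculating with the season-one second-division injury rate, which study one already collects, before the season-two comparison.

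The cost is one paragraph and a less favourable power statement. It needs no extra players and no new data collection.

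### The stated minimum of 217 players contradicts the plan's own inputs: 125 per group with a design effect of 2 is 500 players, and 125 per group fits only a drop of 20 percentage points

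*Combined protocol and SAP*

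**What the plan says.** All the inputs stand in one short paragraph, section 2.4.4.3 of the combined protocol and SAP.

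- Baseline: "about 70% of soccer players in Rwanda sustained injuries", taken from a previous Rwandan study.
- Effect: "To obtain a 20% reduction of injuries with the implementation of the 11+ programme". Whether the 20% is absolute or relative is not stated.
- Power 90% and alpha 5%; sidedness is not stated.
- Result before clustering: "a sample size of 125 in each group (intervention and control) will be required".
- Result after clustering: "Taking into consideration the design effect of 2 for cluster randomization, the minimum number of players that should participate in this study is 217".

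Section 2.4.3 makes the team the unit of randomisation. Section 2.4.4 puts all 19 second-division teams in scope and adds: "The total number of players participating in the in the second division league is 570". That is 19 × 30, and section 2.3.4 gives 30 as the most players a team may register. No intracluster correlation (ICC), assumed cluster size or attrition allowance is given.

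**The concern.** A design effect above 1 must raise the requirement. Here the total falls from 250 (two groups of 125) to 217 once clustering is considered, so the inflation was either not applied or was replaced by some other calculation that the text does not show.

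This matters because 217 is the plan's only recruitment threshold. Section 2.4.4.2 excludes players and coaches who do not agree to take part, and section 2.4.4.1 allows for players or teams leaving, so enrolment below 570 is possible. If it ended anywhere between 217 and 500, the plan as written would describe the trial as having 90% power when it did not.

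The unstated scale of the 20% is a second problem in the same sentence. A reader who takes it as relative will believe that the trial can detect a smaller effect than the calculation supports.

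**Working it through.** **Inputs.** p1 = 0.70; p2 = 0.50 if the 20% is absolute, or 0.70 × 0.80 = 0.56 if relative; power 0.90; alpha 0.05; 125 per group; design effect 2 (all section 2.4.4.3); 19 teams and 570 players (section 2.4.4). Assumed: a two-sided test and equal groups.

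**Step 1: reproduce the 125.** With p̄ the mean of p1 and p2,

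n per group = [1.96 √(2p̄(1−p̄)) + 1.2816 √(p1(1−p1) + p2(1−p2))]² / (p1−p2)².

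- Absolute: (1.96 × 0.6928 + 1.2816 × 0.6782)² / 0.20² = 4.960 / 0.04 = 124.0. The arcsine formula gives 124.1, which rounds up to 125. The plan's figure is reproduced.
- Relative: (1.96 × 0.6828 + 1.2816 × 0.6756)² / 0.14² = 4.858 / 0.0196 = 247.8, that is 248. Not reproduced.

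One-sided versions give 101 (absolute) and 202 (relative), so 125 fits only the two-sided 20-point reading. That is a risk ratio of 0.50/0.70 = 0.71, a 28.6% relative reduction.

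**Step 2: apply the design effect.**

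- Absolute: 125 × 2 = 250 per group; × 2 groups = 500.
- Relative: 248 × 2 × 2 = 992, more than the 570 available.

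**Step 3: look for a route to 217.** None was found.

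- A finite-population correction to 570 gives 250/(1 + 250/570) = 174, or 500/(1 + 500/570) = 266.
- A one-sided, continuity-corrected calculation gives 222 in total (absolute) or 216 per group (relative). Both leave out the design effect and contradict the stated 125.
- If 217 meant players per group (434 in total), power with design effect 2 would be 85.8%.
- If 217 is a total with no design effect, power is again 85.8%.

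**Step 4: power at 217, design effect held at 2.** Effective n per group = 217/2/2 = 54.25.

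- 70% vs 50%: z = (0.20 × √54.25 − 1.96 × 0.6928)/0.6782 = 0.170; power 56.7%.
- 70% vs 56%: z = (0.14 × √54.25 − 1.96 × 0.6828)/0.6756 = −0.455; power 32.5%.

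**Step 5: power at 217 spread over all 19 teams.** If the 2 is assumed to describe squads of 30, the ICC is (2 − 1)/(30 − 1) = 0.034. With 217/19 = 11.4 players per team, the design effect is 1 + 10.4/29 = 1.36 and effective n per group is 108.5/1.36 = 79.8. Then z = (0.20 × √79.8 − 1.358)/0.6782 = 0.632; power about 74% for 70% vs 50%.

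**Step 6: power at 500 and 570, design effect 2.** The t columns use a t reference with 19 − 2 = 17 degrees of freedom and unpooled variance; pooled variance lowers them by about a point.

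| Players | 70 vs 50, normal | 70 vs 50, t | 70 vs 56, normal | 70 vs 56, t |
|---|---|---|---|---|
| 500 | 90.2% | 87.4% | 63.2% | 58.9% |
| 570 | 93.5% | 91.2% | 68.9% | 64.5% |

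**The case against.** The best defence is that 217 is called a minimum, nothing in the plan stops recruitment there, and whole teams are randomised with all 19 in scope. At full enrolment power for the 20-point drop is about 94%, or 91% allowing for few teams. This stands. A reader might infer from the 57% that the trial as intended is underpowered for the effect it was sized on; the documents do not support that.

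A second objection is that 57% depends on holding the design effect at 2 whatever the number of players per team. That fits 217 players drawn from about seven full squads (217/30 = 7.2), whereas the plan describes 19 teams. This also stands: 57% follows from the plan's stated design effect, and about 74% is the figure if the 217 are spread thinly. Neither reaches 90%.

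Third, it is tempting to treat an ICC of 0.034 as the plan's assumption. It is not in the documents. It is a back-calculation from a registration ceiling of 30, and the 2 may be a convention.

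Fourth, 500 itself falls short of 90% once the small number of teams is recognised (about 87%). It is the correct result of the plan's own method, but does not guarantee 90% power.

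Finally, sections 2.3.9 and 2.4.8 compare injury incidence per 1000 hours through rate ratios, not the proportion of players injured. The powers above therefore belong to the endpoint used for sizing, and the corrected text should say so.

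None of this yields 217, and neither blacked-out text nor PDF conversion explains it.

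**Conclusion.** The sample-size statement is wrong as written and must be corrected. The plan's inputs give 500 players, and the stated 217 is less than half of that. Power at 217 is about 57% with the stated design effect, or about 74% under the thin-spread assumption, against a claimed 90%. The 20% reduction is supported only as 20 percentage points; for a 20% relative reduction even all 570 players give about 69% (63 to 65% with a t reference on 17 degrees of freedom).

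The 500 and the comparison with 250 are arithmetic on stated figures. The power figures also rest on a two-sided 5% test (the reading that reproduces 125), equal groups, a correct design effect of 2 except where varied, and the proportion of players injured as endpoint. The finding concerns the documented minimum and power claim. It does not show that a trial enrolling nearly the whole division would lack power for a 20-point drop.

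**What to change.** Rewrite section 2.4.4.3 as follows.

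1. Replace 217 with 500 (250 per group), given as 125 × 2 groups × design effect 2.
2. State the effect as 70% to 50%: 20 percentage points, risk ratio 0.71, two-sided test.
3. Report power for the intended sample of all 19 teams (up to 570 players, design effect 2): about 94% for that effect and about 69% for a 20% relative reduction. Add the figures with a t reference on 17 degrees of freedom: about 91% and 63 to 65%, and about 87% at 500 players for the 20-point drop.
4. Give the basis for the design effect of 2. If it assumes 30 players per team, say so and note that this implies an ICC of about 0.034.
5. State that these figures are for the proportion of players injured.
6. Note that 500/570 is 88% of the registration ceiling, so the 90% claim must be restated if fewer players consent.

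Season-one surveillance can later inform the 70% and the ICC, but section 2.4.4.4 selects teams near the start of 2014-2015, before those data exist, so the check could come before the 2015-2016 intervention season but not before that selection.

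The cost is one rewritten paragraph. No enrolment is added beyond the 19 teams already in scope; the price is a less favourable power statement.

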#### **2.4.4.4 Recruitment and Sampling method**

As there are 19 teams participating in the second division league, a random sampling method was used to obtain the group with nine or ten teams. Random sampling technique will be done to allocate the teams into the groups. Because of the promotion of the first two teams in the first division and the relegation of the last two teams into the second division, the teams will be selected towards the beginning of the season 2014-2015.

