Player exposure forms will then be provided to the coaches and will be requested to record every training time that each player participate in soccer activities. Because coaches are focusing on the game during the match, it could be hectic for them to record match exposure. For this reason, match exposure will be obtained from the reports that are submitted by the referee to the FERWAFA.

Before the beginning of each season the FERWAFA set a deadline for the teams to submit the list of all the players that they will use in the league. Therefore the list of all the players will be obtained from the FERWAFA while additional information pertaining to the study will be requested from the team management.

All the medical personnel of the teams will be invited into the briefing meeting that will be held at the FERWAFA premises to explain to them about the study and their task in the study. They will be explained how to fill the injury report forms and they will be asked to report any injury that will take place during data collection. The injury report and exposure forms will be collected by the researcher or the research assistants after every two weeks.

Training and match exposure as well as injury recording for the main study will commence one week before the first game because training performed during that week is for the preparation of the first game. The first division season will start in September 2014 while the second division season will start in November 2014. The exact dates will be obtained from the FERWAFA after the general assembly meeting preparing the league that will take place after the season 2013-2014. Data collection will take place throughout the season up to the last game. Because the FERWAFA allows the teams to recruit new players during the mid season, players who will join the teams halfway through will be recorded from the period recruited. The season will end in June 2015 for the first division and May 2015 for the second division. At the end of the season, the last two teams from the first division are relegated to the second division while the first two teams in the second division are promoted to the first division. A period of rest is given to the

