teams and players at the end of the season 2014-2015 which allows teams to reorganize and recruit new players. Changes that will take place during this period will be noted and appropriate actions will be done to allow the injury surveillance to continue in the subsequent season. The study two with intervention will commence at the beginning of the season 2015-2016.

Figure 2: Study one framework

[figure not shown]

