## **2.4.7 Procedure**

### **2.4.7.1 Data collection**

Ethical approval, permissions and consent would be obtained during season one before conducting the study. Translation of the questionnaires into Kinyarwanda will be done before the pilot study. The translated questionnaires will be piloted among licensed five soccer coaches at school level to assess for clarity and responsiveness. A meeting will be held with them to discuss any unclear question from the translated versions and possibilities for better refining them.

During the preseason period, questionnaires assessing the knowledge of coaches regarding injury prevention will be distributed to coaches and appointment will be made for collection of the filled questionnaire. Questionnaires will be collected either by the researcher or the research assistants. Information pertaining to the availability of the medical personnel will also be obtained from the questionnaires.

Because of the changes that might take place at the end of the first season, coaches will again be invited to answer the knowledge questionnaires that will be distributed to them during the preseason period. Any other changes that will take place will also be noticed before the start of the season 2015-2016 as to the arrival of the new or change of the coaches, new teams registering into the second division league or new medical personnel arriving into the teams.

During the preseason period, July-August 2015, all the head, assistants and goalkeeper coaches of the teams in the intervention group in the second division will be invited to the training. The first part of the training will be conducted in two days where they will be taught about injury prevention in general and more specifically the importance and the use of the “11+” warm up programme. The first day will be for introduction and theoretical explanation of the conduct of the “11+” exercises while the second day will be reserved for practical demonstrations. The training will be provided by the researcher. Coaches will also be introduced to the recording of the use of the exercises while in the teams. The recording will be emphasized to ensure compliance. At the end of the training, the coaches will be provided DVDs, pamphlets and the FIFA link (where they could download the materials for free) of the exercises and will be

requested to use the “11+” as the warm up programme at least three times a week and before each match that the team will play.

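### Section 2.4.4.4 dates team selection before the promotion and relegation round that it gives as its reason, so as written 2 of the 19 teams in the intervention season would have no random allocation

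*Combined protocol and SAP*

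**What the plan says.** Study two is a cluster-randomised trial "with teams as units of randomization" (2.4.3). On the number of clusters, 2.4.4 states: "There are 19 teams in the second division".

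On allocation, 2.4.4.4 says "Random sampling technique will be done to allocate the teams into the groups". The next sentence gives promotion and relegation as the reason why "the teams will be selected towards the beginning of the season 2014-2015". No other date for forming the groups appears in the text.

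On the calendar, 2.3.6.1 has the second-division season running from November 2014 to May 2015 and the first-division season ending in June 2015. It then says that "the last two teams from the first division are relegated to the second division", while two second-division teams go up. The same section adds: "The study two with intervention will commence at the beginning of the season 2015-2016". Coach training is placed in July-August 2015 by 2.4.7.1 and in October 2015 by 2.4.6.

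On teams that move, 2.4.4.1 says "Players or teams that will leave or join the league before the end of the study will be included in the analysis", limited to the time they take part. Section 2.4.7.1 says that newly registered teams will be noted before 2015-16. Section 2.3.6.1 promises suitable action after the off-season changes, but only so that surveillance can continue.

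**The concern.** The stated reason and the stated date conflict. Promotion and relegation are a reason to wait until a round is settled. Selection at the start of 2014-15 comes before the round that fixes which teams play in the intervention season.

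The teams that enter are the difficulty. They hold no random assignment, yet 2.4.4.1 brings joining teams into the analysis. If the researcher chose their arm, or if they became controls by default because no training invitation was addressed to them, the between-arm comparison would no longer be fully randomised.

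Relegated teams are also unlikely to resemble the rest. First-division teams play 26 matches against 11 to 12 in the second division (2.3.4), and 2.4.4 describes them as having medical personnel. Exposure and medical support both bear on how injuries occur and are recorded. The before-after objective (2.4.2.1 a) is affected too: an entrant's season one was played in the first division, and a promoted team has no second-division season two.

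**Working it through.** **Order of events as printed**

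1. Team selection: towards the start of 2014-15 (2.4.4.4). The second division starts in November 2014.
2. Season one ends: May 2015 (second division) and June 2015 (first division). Two teams go up and two come down (2.3.6.1).
3. Coach training: July-August 2015 (2.4.7.1) or October 2015 (2.4.6).
4. Intervention season: 2015-16.

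From November 2014 to July or October 2015 is about 8 to 11 months, and one exchange of teams falls inside that gap. Both training dates come after the exchange, so the disagreement between them does not change the result.

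**Team counts** (assuming the league stays at 19 teams)

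- Allocated teams that leave before any intervention: 2/19 = 10.5%.
- Allocated teams that remain: 19 − 2 = 17.
- Teams in 2015-16 with no allocation: 2/19 = 10.5%.
- With randomisation after the exchange: 19 of 19 allocated, 0 unallocated.

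**Does losing two teams matter for power?** Section 2.4.4.3 assumes 70% injured, a 20% reduction, 90% power, 5% alpha and a design effect of 2. Sidedness is not stated; I take it as two-sided. The standard formula is

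n = [1.96 √(2p̄(1−p̄)) + 1.2816 √(p₁(1−p₁) + p₂(1−p₂))]² / (p₁ − p₂)².

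Reading the reduction as absolute (0.70 to 0.50, p̄ = 0.60): [1.96 × 0.6928 + 1.2816 × 0.6782]² / 0.04 = 124 per group, which agrees closely with the plan's 125. Reading it as relative (0.70 to 0.56) gives 248, which does not.

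Section 2.4.4 gives 570 players, or 570/19 = 30 per team. Two teams are 60 players, leaving 510. Assuming equal arms, dividing by 2 arms and by the design effect of 2 gives effective sizes of 142.5 and 127.5 per arm.

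| Reduction | Power, 570 players | Power, 510 players |
|---|---|---|
| 70% to 50% (matches the plan's 125) | 93.5% | 90.8% |
| 70% to 56% (relative reading) | 68.9% | 64.0% |

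The loss costs about 3 to 5 percentage points of power. That is a loss of precision, not bias.

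**What the text leaves open.** Sections 2.3.6.1, 2.4.4.1, 2.4.4.4 and 2.4.7.1 are the places that deal with changing teams. None of them says how an entering team gets an arm, or what becomes of a promoted team's allocation.

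**The case against.** The best reply is that the year is a slip. The reason given in 2.4.4.4 fits selection after the mid-2015 round, just before the 2015-16 intervention. If 2015-2016 was meant, no allocated team is lost to that round and no unallocated team enters through it. The reply is plausible and may well be right, but it still leaves a wrong date on the randomisation step. A third reading, that the sentence refers to the round before 2014-15, leaves the mid-2015 round unhandled.

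Two further cautions also stand. The dated sentence speaks of selecting teams, not allocating them; that it dates the allocation is inferred from its place directly after the allocation sentence. Figure 3 is not available to me and might show the timing. And 2.4.4.1 is a time-at-risk rule: it does not say outright that unrandomised teams enter the between-arm comparison, though nothing excludes them.

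A reader might infer more than the documents support:

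- *Losing the strongest teams biases the trial.* Promotion is settled before any coach is trained, so the intervention cannot influence it. The population narrows, but the comparison among the remaining teams is not biased by this alone.
- *Both promoted teams could come from one arm.* With arms of 10 and 9, and promotion unrelated to arm, the chance is 162/342 = 47%. But 90/342 = 26% of this leaves 8 vs 9, as balanced as the start. Only 72/342 = 21% leaves 10 vs 7, and unequal numbers are not bias.
- *Allocation precedes consent.* Section 2.4.7.1 says "Ethical approval, permissions and consent would be obtained during season one before conducting the study", but 2.3.6.1 puts coaches' written consent in preseason, and 2.4.9 says study two needs no special consent. The order is unclear, not shown to be wrong.
- *Season-one recording is biased by knowledge of the arm.* The researcher is unblinded, but nothing says that teams learn their arm during season one, and 2.4.4.5 keeps the research assistants blind.

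**Conclusion.** The point holds in limited form. As printed, 2.4.4.4 sets the only date for forming the groups before the exchange of teams it cites as its reason. Two of 19 allocated teams (10.5%) would leave before the intervention, at a modest cost in precision. Two of the 19 teams in 2015-16 (10.5%) would have no random allocation, with no rule for their arm and an inclusion rule that does not keep them out of the comparison. The entrants are the threat to validity; the departures are not.

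This rests on three assumptions: that the selection date is the allocation date, that 2014-2015 is the intended year, and that the league stays at 19 teams with two up and two down. Because the year may be a slip, I hold the design flaw itself with only moderate confidence. That the date needs correcting does not depend on which reading is right.

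**What to change.** In 2.4.4.4, replace the dated sentence with a statement that teams are randomised once, after the 2014-15 promotions and relegations are final and the 2015-16 second-division list is registered, and before coach training invitations go out.

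In 2.4.4.1, limit the between-arm comparison to randomised teams, each analysed in its allocated arm for its time at risk. Report any team that joins without random allocation descriptively, outside that comparison.

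Reconcile the July-August and October 2015 training dates in 2.4.7.1 and 2.4.6, so that the window for randomisation is clear.

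The cost is protocol wording. The sample, staff and data collection do not change. The one practical condition is that the team list be registered before invitations are sent. The documents give no date for that registration, so it should be checked against whichever training date is kept.
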